### Sample size

Intraclass correlation was calculated based on preliminary data (214 individuals) across the recruited 40 sites and was found to be 0.16 for the BMI *z* score. To detect a between-group difference of 0.24 (±0.43) in the BMI *z* score (based on outcome data from a previous Australian RCT examining 12-month weight loss outcomes in children) [12], 12 participants from each of the 40 sites (20 intervention, 20 control) are required to achieve 80 % power based on an alpha of 0.05.

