### Targeted programs to address childhood obesity

Community-based weight management programs are an important response to address childhood overweight and obesity. International recommendations identify that the core elements of any initiative to address the widespread problem should involve the family and include nutrition education, promote physical activity and include strategies that target behavior modification [2, 7–9]. Two recent Australian randomized controlled trials (RCTs), namely PEACH (*n* = 169) [10] and HIKCUPS (*n* = 165) [11] highlight the importance of engaging and targeting parents in structured weight loss programs for overweight/obese children aged 5 to 9 years old. Another RCT (*n* = 111) found that a parent-directed approach based on parenting skills training with lifestyle education improved BMI z scores by approximately 10 % compared to approximately 5 % with parenting-skills training alone or wait-listing for intervention [12]. This study demonstrates the importance of including parents in strategies aimed at improving weight management in children. Although, the specific behaviors required for effective weight loss are well established, the challenges associated with the behavior change aspects of interventions are profound; therefore, for these and many other reasons, trials are often not upscaled and translated into a real-world context [9, 13, 14].

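### The planning difference of 0.24 is hard to reconcile with the article's own summary of the trial it is taken from, and the stated 80 % power does not follow from the stated inputs

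*Protocol article*

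**What the plan says.** The protocol article, under Sample size, gives the only justification for the trial's size. The target is given as "To detect a between-group difference of 0.24 (±0.43) in the BMI" z score and attributed to reference 12, described there as an earlier Australian trial with 12-month weight outcomes in children. The ±0.43 carries no label. The intraclass correlation, from preliminary data on 214 individuals, "was found to be 0.16 for the BMI" z score. The conclusion is that "12 participants from each of the 40 sites (20 intervention, 20 control) are required" for 80 % power at an alpha of 0.05.

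The Background, under Targeted programs to address childhood obesity, describes reference 12 in other terms: a parent-directed approach combining parenting skills with lifestyle education "improved BMI z scores by approximately 10 % compared to approximately 5 % with parenting-skills training alone or wait-listing for intervention". No time point and no baseline BMI z score are given for these percentages.

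**The concern.** Both sections describe the same trial. If its active arm improved by about 10 % and its comparators by about 5 %, its between-group contrast is about 5 % of baseline BMI z. At baseline values one might assume for overweight or obese children, that is well below 0.24. The figure of 0.24 looks more like the change in one arm.

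The stake is how the result will be read. The article says the trial is meant to inform policy and program delivery. A reader told that it had 80 % power for a difference seen in a previous trial could take a non-significant result as evidence against incentives. If the source contrast is nearer 0.10 to 0.15, the chance of detecting it could be much lower than the paragraph implies.

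**Working it through.** **Inputs from the Sample size section.** Difference 0.24; ±0.43, read as an SD (an assumption, since it is unlabelled); ICC 0.16; 20 sites per arm; 12 children per site (240 per arm); alpha 0.05, taken as two-sided (not stated).

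**Step 1. The plan's own figure.**
- Design effect = 1 + (12 − 1) × 0.16 = 2.76.
- Effective sample size per arm = 240 / 2.76 = 87.
- SE of the difference = 0.43 × √(2 × 2.76 / 240) = 0.0652.
- Power at 0.24: 95.7 % by normal approximation, 94.8 % by noncentral t with 2 × 20 − 2 = 38 df.

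The stated 80 % is not reproduced. Nine measured children per site (25 % loss) still gives 93 % to 94 %. About 4 children per site, or about 12 to 13 sites per arm of 12, would give 80 %. At the stated size, 80 % power at 0.24 would need an SD of about 0.55 (t) to 0.56 (normal).

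**Step 2. Difference detectable with 80 % power on the stated inputs.**
- Normal: (1.96 + 0.8416) × 0.0652 = 0.183.
- Noncentral t, 38 df: 0.187.

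**Step 3. Can 0.24 be the contrast described in the Background?** Divide 0.24 by the fractional improvement to get the mean baseline z it implies.

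| Reading of 0.24 | Calculation | Implied baseline z |
|---|---|---|
| Between-arm, 10 % − 5 % | 0.24 / 0.05 | 4.8 |
| Between-arm, widest gap if rounded to whole numbers (10.5 % − 4.5 %) | 0.24 / 0.06 | 4.0 |
| Between-arm, limiting gap if rounded to the nearest 5 % (12.5 % − 2.5 %) | 0.24 / 0.10 | 2.4 |
| Within-arm, 10 % | 0.24 / 0.10 | 2.4 |

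**Step 4. Power for a 5-point contrast.** The documents give no baseline z, so 2.0 to 3.0 is assumed; the contrast is then 0.05 × 2.0 = 0.10 to 0.05 × 3.0 = 0.15. SD 0.43 and 20 × 12 per arm are kept. The second ICC, 0.05, is an assumption to show sensitivity: design effect 1 + 11 × 0.05 = 1.55, SE = 0.43 × √(2 × 1.55 / 240) = 0.0489. Power is by noncentral t, 38 df.

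| Baseline z (assumed) | Difference | Power, ICC 0.16 | Power, ICC 0.05 |
|---|---|---|---|
| 2.0 | 0.10 | 32 % | 51 % |
| 2.4 | 0.12 | 43 % | 67 % |
| 3.0 | 0.15 | 61 % | 85 % |

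Using the planned 570 children (570 / 40 = 14.25 per site) at ICC 0.16 moves the range only to 33 % to 63 %.

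**The case against.** A reader might infer that 0.24 cannot be a between-group difference. The documents do not support that. The Sample size section calls it one explicitly. The step from percentages to z units needs the cited trial's baseline z, which is not given. Both percentages are approximate, no time point is attached to them, and the article does not say whether they are raw or adjusted. With rounding to the nearest 5 %, the gap could approach 10 points, and 0.24 would then fit a baseline near 2.4. Nor does the ± format settle the matter, since a planning difference is often written beside its assumed SD. All of this stands, and it limits the claim to a conflict that needs explaining.

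A reader might also infer that true power is a third to 60 % in place of a correct 80 %. That does not hold either. The 80 % is not the right value at 0.24 in the first place. The lower range depends on applying an ICC reported for BMI z score to a ±0.43 that may be the SD of a change. The primary outcome is change in BMI z, analysed with baseline adjustment, so its ICC may differ; at 0.05 the range rises to 51 % to 85 %.

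Finally, a trial may legitimately target a larger difference than its source observed. That is true, but it has to be justified as such. Here the figure is presented as coming from the source.

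**Conclusion.** The point holds in two parts.

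First, the two accounts of reference 12 are hard to reconcile, and a within-arm change may have been entered as the between-arm difference. This is not proven; only the cited trial's arm-level results can settle it.

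Second, the stated 80 % does not follow from the stated inputs, which give about 95 % at 0.24 and 80 % at about 0.18 to 0.19. This needs no figure from outside the documents, only the reading of ±0.43 as an SD and a two-sided test.

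The power for a 5-point contrast (32 % to 61 % at ICC 0.16, 51 % to 85 % at ICC 0.05) is conditional on an assumed baseline z of 2.0 to 3.0 and on SD 0.43. The higher power at 0.24 does not remove the concern, because the detectable difference of about 0.19 still exceeds 0.10 to 0.15 at the stated ICC. The paragraph is the basis for judging what the trial can detect and should be corrected.

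**What to change.** Revise the Sample size paragraph as follows.

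- State whether 0.24 is a within-arm change or a between-arm difference, and label the ±0.43.
- Replace 0.24 with the between-arm contrast from reference 12, or justify 0.24 on other grounds without attributing it to that trial.
- Correct the 80 % figure so that it follows from the stated SD, ICC and number of sites, or state the inputs that produce it.
- At the fixed size, restate the power for the chosen difference and the difference detectable with 80 % power (about 0.19 on the stated inputs).

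The cost is one reworded paragraph. Enrolment and conduct do not change. The downside is that the stated power for the source's contrast is likely to be less favourable.

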## Methods/Design

### Study design

The study is a cluster RCT (Fig. 1) delivered within the context of the existing Go4Fun program with 10 week, 6 month, and 12 month follow-up (*n* = 40 sites, 570 participants), which compares the effectiveness of participation in the standard Go4Fun program with an enhanced goal setting and structured incentive scheme (intervention) versus participation in the existing Go4Fun program (control). Individual randomization is not possible given the nature of the intervention, so randomization by site will be conducted. Building on our existing research platform, we propose a pragmatic and feasible trial to determine the effectiveness, acceptability, and sustainability of the enhanced intervention at 6 and 12 months after the program. The CONSORT statements for cluster RCTs [43] and for nonpharmacological interventions [44] will be followed.

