### Randomization

Eligible sites have been randomized to either deliver the intervention (standard Go4Fun plus incentives) or control (standard Go4Fun) program for 10 weeks. Randomization was conducted using a computer-generated sequence (1:1) managed by the research team based at The George Institute and independent of the Department of Premier and Cabinet NSW (DPC), any program leader or LHD. Clusters were stratified according to local health district to ensure equal representation across groups within each LHD.

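### The sample-size inputs as printed give about 95 % power, not the stated 80 %, if ±0.43 is the standard deviation and the test is two-sided

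*Protocol article*

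**What the plan says.** The Sample size section of the protocol article gives a nearly complete set of inputs for the primary outcome.

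- ICC, from preliminary data on 214 individuals: it "was found to be 0.16 for the BMI *z* score".
- Target effect, taken from an earlier Australian trial: "To detect a between-group difference of 0.24 (±0.43) in the BMI *z* score". The section does not say what the ±0.43 is.
- Conclusion: "12 participants from each of the 40 sites (20 intervention, 20 control) are required to achieve 80 % power", at an alpha of 0.05. Whether the test is one- or two-sided is not stated.

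The Randomization section confirms equal allocation by site. The Statistical analysis section says that the models will account for between-cluster variance, so a calculation with a design effect matches the planned analysis. Elsewhere, the Study design section gives the size of the trial as "40 sites, 570 participants".

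**The concern.** A reader who puts the printed inputs into the standard cluster formula does not get 80 %. Either one of the inputs is not the one used, or the claim that 12 children per site are needed for 80 % power is wrong.

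This is the article's only power statement for the primary outcome. If the inputs are right, the trial can detect a smaller difference with 80 % power than the 0.24 it names, and its sensitivity is understated. If the SD or ICC actually used was larger, the published value is wrong, and anyone who borrows it for a similar trial would plan too small a study.

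**Working it through.** **Inputs** (Sample size section): difference d = 0.24; SD = 0.43 (assumed meaning of the ±); ICC = 0.16; m = 12 per site; k = 20 sites per arm; alpha = 0.05 (two-sided assumed).

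**Attempt to reproduce the stated 80 %**

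1. Design effect = 1 + (m − 1) × ICC = 1 + 11 × 0.16 = 2.76.
2. Children per arm = 20 × 12 = 240; effective number per arm = 240/2.76 = 87.0.
3. Standard error of the difference = SD × √(2 × 2.76/240) = 0.43 × √0.0230 = 0.0652.
4. d/SE = 0.24/0.0652 = 3.68.
5. Normal power = Φ(3.68 − 1.96) = Φ(1.72) = 95.7 %.
6. Noncentral t with 2 × (20 − 1) = 38 degrees of freedom: 94.8 %.

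The stated figure is not reproduced. The gap is about 15 percentage points.

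**What 80 % would need on the same inputs**

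- Individually randomized n per arm = 2 × 0.43² × (1.960 + 0.842)²/0.24² = 50.4, rounded up to 51.
- With clustering: 51 × 2.76 = 140.8 per arm, and 140.8/12 = 11.7 sites per arm. In whole sites, 12 per arm gives 81.3 % (normal) or 77.8 % (t), and 13 per arm gives 84.3 % or 81.2 %.
- With all 40 sites kept and 4 children each: design effect 1 + 3 × 0.16 = 1.48, SE = 0.43 × √(2 × 1.48/80) = 0.0827, ratio 2.90, power 82.7 % (normal) or 80.7 % (t).

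**Which single input would have to change to give 80 % at 12 × 40**

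| Input | Printed | Needed (t to normal, or the reverse) |
|---|---|---|
| SD | 0.43 | 0.55 to 0.56 |
| ICC | 0.16 | 0.32 to 0.34 |
| Difference | 0.24 | 0.18 to 0.19 |

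Check on the difference by the normal formula: 2.802 × 0.0652 = 0.183; by t it is 0.187.

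**Other readings tried** (normal formula unless stated)

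| Variant | Power |
|---|---|
| One-sided alpha 0.05 | 97.9 % |
| Design effect 1 + m × ICC | 94.7 % |
| Cluster-size coefficient of variation 0.3 / 0.5 / 0.7 | 94.6 % / 92.5 % / 88.8 % |
| 20 % of the 12 per site lost | 94.4 % (t: 93.3 %) |
| 50 % lost, so 6 per site | 89.7 % (t: 88.1 %) |
| SD multiplied by √2 | 74.0 % (t: 71.8 %) |
| 20 sites in total instead of 40 | 74.0 % (t: 69.2 %) |

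None of these gives 80 %.

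**The case against.** The strongest objection is that the result depends on an unlabelled figure. The article never calls 0.43 a standard deviation, and its source is not at hand. With an SD of about 0.55 the stated 80 % would be right, and with 0.43 × √2 the power would fall below it. This stands, and the finding is therefore conditional. It does not remove the problem: a spread printed beside the difference in a power statement will be read as the SD, and on that reading the sum does not work.

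A second objection is that nothing is at risk, because the printed inputs imply more power than claimed. The direction is indeed conservative, and this stands against any suggestion of an underpowered trial. It limits the consequence, but the figure still does not follow from its inputs.

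A third is that an unstated allowance for drop-out explains the gap. The arithmetic is against it. Losing half of every site still leaves 88 to 90 %, and coming down to about 80 % means about 4 of 12 children remaining per site.

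A reader might also infer a contradiction between the 12 × 40 = 480 children required and the 570 planned. The documents do not support that. The 480 is a required minimum. The recruitment section for sites expects 12 to 15 children per site per term, which is 480 to 600 over 40 sites, and 570 lies inside that range. An attrition allowance is also something that a condensed article commonly leaves to the full protocol.

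**Conclusion.** The point holds as an error in the stated power. On the printed inputs, with ±0.43 read as the SD and a two-sided test, 12 children at each of 40 sites give about 95 % power (94.8 to 95.7 %) for a difference of 0.24. It follows that 12 per site are not required for 80 %. At that size the trial has 80 % power for a difference of about 0.18 to 0.19.

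The text does not show whether the SD, the ICC, the difference or the power figure itself is at fault. Nor does it show that the trial is underpowered. It would be tempting to go further and treat the ratio 480/570 as a planned loss of about 16 %, or to take 12 per site as the number analysed at 12 months. The article states neither.

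This is a correction to a reported figure. It changes no outcome, number of sites or analysis.

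**What to change.** First, say what the ±0.43 is and whether alpha is two-sided. Then take one of two routes:

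- **If the printed inputs were the ones used:** restate the result as about 95 % power for a difference of 0.24, and 80 % power for about 0.18 to 0.19, with 12 children per site in 40 sites. Remove the claim that this number is required for 80 %.
- **If a different SD, ICC or difference was used:** print that value in place of the present one and confirm that the calculation then returns 80 %.

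No loss-to-follow-up percentage, and no statement that 12 per site means children analysed at 12 months, should be added unless the sponsor confirms it.

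The cost is wording only, plus retrieving the original calculation.

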### Statistical analysis

Analysis will be conducted at the individual level and will follow the intention-to-treat principle. The control and intervention groups will be compared on baseline characteristics using independent t-tests for continuous variables or chi square tests for categorical variables. For the primary outcome, the mean difference in BMI *z* score at 12 months between control and intervention groups will be analyzed after adjusting for the baseline characteristics using regression models. Similar regression models will be used for the secondary outcomes. These models will account for the between-cluster variance and will be adjusted for baseline characteristics. All analyses will be undertaken using SAS 9.4 for Windows (SAS Institute Inc. Cary, NC, USA), and statistical significance will be set at *P* < 0.05.

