### Eligibility/recruitment: Sites (namely programs where Go4Fun is delivered)

To be eligible to participate in the trial, sites must meet the following criteria:Are delivering the standard Go4Fun program in 2015;Show a 2014 attendance average of at least 10 children enrolled per program per term; andAre willing to participate in a trial and adhere to standardized procedures for the duration of the trial.

For site recruitment, all NSW LHDs (where Go4Fun is delivered) were invited to participate, 40 programs agreed to participate, and ethical approval was secured from the relevant LHDs. Based on prior process evaluation work [17] and from prior attendance records, the recruited sites are likely to enroll an average of 12 to 15 children per site per term. Local program leaders will assess eligibility, obtain informed consent, and conduct baseline study visits, and research assistants will conduct the follow-up assessments. Previous RCTs conducted by the research team have underscored the critical importance of site-based program leader involvement and engagement to maximize downstream sustainability.

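### The baseline t-tests and chi-square tests ignore site clustering: for BMI z score the nominal 5 % test could be falsely significant up to about 24-27 % of the time

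*Protocol article*

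**What the plan says.** The Study design section states that "randomization by site will be conducted", and the Randomization section adds that allocation was 1:1 and stratified by local health district (LHD). The Sample size section reports an ICC that "was found to be 0.16" for BMI z score, from preliminary data on 214 children across the 40 sites.

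The Statistical analysis section opens with "Analysis will be conducted at the individual level". It then says that the two groups will be "compared on baseline characteristics using independent t-tests for continuous variables or chi square tests for categorical variables". No allowance for clustering is mentioned there. Clustering appears only later in the section, where the regression models for the primary and secondary outcomes are said to take variation between clusters into account. That statement refers to those models and does not reach back to the baseline tests.

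**The concern.** An independent t-test or chi-square test takes its standard error from the number of children. In this trial, chance differences between arms arise from allocating 40 sites, and children at the same site resemble one another. The standard error is therefore too small, and ordinary chance differences between sites are declared significant too often. The plan deals with this for outcomes but names tests for baseline that do not.

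What is at stake is how the baseline table is read. The article describes sites as already randomized, while local program leaders are still to assess eligibility and obtain consent. This wording suggests, without saying so outright, that children join after their site's allocation is fixed. Readers will then look to the baseline table for signs that the arms recruited different children. A test with an inflated false-alarm rate on the key variable cannot separate such recruitment from chance differences between sites.

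**Working it through.** The article states no error rate for the baseline tests, so there is no figure of its own to reproduce. The calculation takes only the ICC, the site size and the significance level from the plan. (The 80 % power in the Sample size section does not reproduce from its own inputs: the design effect of 2.76 below leaves 240/2.76 = 87 effective children per arm and about 96 % power for a difference of 0.24 with SD 0.43. That is a separate matter and does not enter here.)

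**Inputs**
- ICC 0.16 for BMI z score (Sample size). It is assumed to apply to the baseline value; the article does not say whether it refers to level or change.
- Children per site, m: 12 (Sample size); 570/40 = 14.25, from "40 sites, 570 participants" (Study design); 15 as the upper end of sites being "likely to enroll an average of 12 to 15 children per site per term".
- 20 sites per arm (Sample size).
- Significance level 0.05 (Statistical analysis), assumed two-sided.

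**Step 1: understatement of the variance.** Design effect DE = 1 + (m - 1) x ICC. At m = 12, DE = 1 + 11 x 0.16 = 2.76, so the standard error is too small by a factor of sqrt(2.76) = 1.66.

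**Step 2: true false-positive rate of the nominal 5 % test.** Rate = 2 x [1 - Phi(1.96/sqrt(DE))].

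| m | DE at ICC 0.16 | True rate |
|---|---|---|
| 12 | 2.76 | 23.8 % |
| 14.25 | 3.12 | 26.7 % |
| 15 | 3.24 | 27.6 % |

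A simulation (20,000 runs, 20 equal-sized sites per arm, ICC 0.16) agrees: t-test 23.6 % at m = 12 and 27.1 % at m = 14; chi-square test about 24 % at m = 12.

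**Step 3: other baseline variables.** The article gives no ICC for them. Over an assumed range, with m = 12:

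| Assumed ICC | DE | True rate |
|---|---|---|
| 0.01 | 1.11 | 6.3 % |
| 0.02 | 1.22 | 7.6 % |
| 0.05 | 1.55 | 11.5 % |
| 0.10 | 2.10 | 17.6 % |

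**Step 4: effect of stratifying by LHD.** Suppose a share f of the site variance lies between LHDs and is balanced by the stratification. DE is then replaced by m x (1 - f) x ICC + (1 - ICC). With m = 12 and ICC 0.16:

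- f = 0: 1.92 + 0.84 = 2.76, rate 23.8 %
- f = 0.25: 1.44 + 0.84 = 2.28, rate 19.4 %
- f = 0.5: 0.96 + 0.84 = 1.80, rate 14.4 %
- f = 0.75: 0.48 + 0.84 = 1.32, rate 8.8 %
- f = 1: 0 + 0.84 = 0.84, rate about 3 %

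The article gives no information on f.

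**The case against.** The strongest reply is that this is a descriptive step with no route into the trial's conclusions. The outcome models allow for clustering, and neither the primary nor the secondary tests use the baseline P values. That stands: a reader might infer that the primary comparison is invalid, and the text does not support this.

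A reader might also infer that about one baseline comparison in four will be falsely significant. That does not follow. The ICC of 0.16 belongs to BMI z score alone, and it is imprecise, coming from 214/40 = about 5 children per site. Stratification by LHD could lower the rate further, so 24-27 % is the upper end at that ICC.

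A third tempting reading is that these P values will decide which covariates enter the models. The article does not say so. Adjustment for the baseline characteristics can equally mean the whole set, whatever the tests show, and naming the covariates is detail that may properly sit in the statistical analysis plan.

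Finally, it can be said that baseline comparison has a purpose where children are recruited after site allocation. That is fair, and it is why a test need not be ruled out altogether. But the purpose calls for a test with the right error rate, which the named ones do not have. None of these replies removes the mismatch between the stated tests and the design.

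**Conclusion.** The point holds, limited to the baseline comparison. The named tests assume independent children in a trial that randomized sites. For BMI z score the nominal 5 % test has a true false-positive rate of up to about 24 % (12 per site) to 27 % (14.25 per site). This rests on the plan's ICC of 0.16 applying to the baseline value, equal site sizes, a two-sided test, and no site variance absorbed by the LHD strata; if half were absorbed, the rate at 12 per site would be 14.4 %. For other variables the rate is unknown, and about 6-18 % over the assumed ICC range of 0.01 to 0.10. The consequence is a baseline table whose P values could wrongly suggest imbalance or differential recruitment. Distorted covariate selection is a risk to guard against, not something the article plans.

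**What to change.** Replace the sentence on t-tests and chi-square tests with one stating that baseline characteristics will be summarized by arm at child and site level, without P values. If a test is kept, for instance to look for differential recruitment, it should allow for site clustering, for example through the same site random-effect model as is used for the outcomes. Add that baseline P values will not be used to choose adjustment covariates.

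The cost is one sentence, and the descriptive option means less analysis. The Trial status section says that data cleaning and analysis had not begun at submission, so a change at that stage would have been made without knowledge of results.
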